# Organisational models supported by technology for the management of diabetic disease and its complications in a diabetic clinic setting: study protocol for a randomised controlled trial targeting type 2 diabetes individuals with non-ideal glycaemic values (Telemechron study)

**DOI:** 10.1186/s13063-023-07515-6

**Published:** 2023-08-10

**Keywords:** Type 2 diabetes mellitus, Technology, Telemedicine, mHealth, Mobile application, Smartphone

## Abstract

**Introduction:**

Type 2 diabetes mellitus (T2DM) is a non-communicable disease representing one of the most serious public health challenges of the twenty-first century. Its incidence continues to rise in both developed and developing countries, causing the death of 1.5 million people every year. The use of technology (e.g. smartphone application—App) in the health field has progressively increased as it has been proved to be effective in helping individuals manage their long-term diseases. Therefore, it has the potential to reduce the use of health service and its related costs. The objective of this study is to evaluate the impact of using a digital platform called “TreC Diabete” embedded into a novel organisational asset targeting poorly controlled T2DM individuals in the Autonomous Province of Trento (PAT), Italy.

**Methods:**

This trial was designed as a multi-centre, open-label, randomised, superiority study with two parallel groups and a 1:1 allocation ratio. Individuals regularly attending outpatient diabetes clinics, providing informed consent, are randomised to be prescribed TreC Diabete platform as part of their personalised care plan. Healthcare staff members will remotely assess the data shared by the participants through the App by using a dedicated online medical dashboard. The primary end-point is the evaluation of the Hb1Ac level at 12-month post-randomisation. Data will be analysed on an intention-to-treat (ITT) basis.

**Discussion:**

This trial is the first conducted in the PAT area for the use of an App specifically designed for individuals with poorly controlled T2DM. If the effects of introducing this specific App within a new organisational asset are positive, the digital platform will represent a possible way for people diagnosed with T2DM to better manage their health in the future. Results will be disseminated through conferences and peer-reviewed journals once the study is completed.

**Trial registration:**

ClinicalTrials.gov NCT05629221. Registered on November 29, 2022, prior start of inclusion.

**Supplementary Information:**

The online version contains supplementary material available at 10.1186/s13063-023-07515-6.

## Administrative information

**Table Taba:** 

**Title {1}**	Organisational models supported by technology for the management of diabetic disease and its complications in a diabetic clinic setting. Study protocol for a randomised controlled trial targeting type 2 diabetes individuals with non-ideal glycemic values (Telemechron study)
**Trial registration {2a and 2b}**	ClinicalTrials.gov NCT05629221 [Registered on November 29, 2022 prior start of inclusion]
**Protocol version {3}**	Version 2 of 27–09-2022 First issue date: 11 May 2022 (8 August 2022) Approved by Ethics Committee: 30 May 2022 (Amendment: 27 September 2022) (Ethics Committee opinions are available as Additional File 1) Primary reason for amendment: The trial initially aimed to recruit T2DM individuals with non-ideal glycemic values, also affected by post-infarction cardiomyopathy and/or heart failure. It was soon realised that the criteria of being both diabetic and with a heart condition would have compromised the recruitment process and no targeted sample size would have been reached in time. Therefore, the following two inclusion criteria were removed: (1) having a diagnosis of ischemic heart disease identified by a previous documented acute ischemic event requiring an hospital access or a diagnosis of ischemic heart diseases following a positive test for inducible ischemia, or (2) having a diagnosis of heart failure with a New York Heart Association (NYHA) Classification of Heart Failure I or II or III (reduced or preserved ejection fraction) [1] defined on the basis of a previous hospitalisation for heart failure, or defined by an ejection fraction below 50% and NYHA I or II or III (absence of dyspnoea at rest) Before the first version of the protocol was approved, Ethical Committee made the following requests: i) improved description of the intervention; ii) clarification related to the Regulation (EU) 2017/745 of the European Parliament and of the Council of 5 April 2017 on medical devices, that is, clarifying that TreC Diabete is not a medical device [2]; iii) amendment to the informed consent form to further simplify the wording (available in English upon request)

## Introduction

### Background and rationale {6a}

Diabetes is a non-communicable disease characterised by an elevated level of blood glucose. About 422 million people have diabetes worldwide [3]; with 1.5 million deaths every year, diabetes is the fifth cause of death and represents one of the most serious public health challenges of the twenty-first century [3]. The most common type of diabetes, type 2 diabetes mellitus (T2DM), accounts for 90% of all diabetes cases. It is often described as a lifestyle disease because of its association with modifiable risk factors, such as overweight and physical inactivity. According to the World Health Organization (WHO), the incidence of T2DM is expected to rise in both developed and developing countries, leading to an increase in the economic loss for the people affected by the diseases, the society and the health systems [3]. Considering that diabetes is one of the main causes of severe long-term conditions, such as cardiovascular events, macro- and micro-vascular complications, it is urgent to tackle it by either preventing its onset or delaying its progression [4].

The management of diabetes is a sensitive issue, particularly when considering the (perceived) quality, acceptability and easiness of the service delivery, both from a patient and healthcare staff’s perspective [5]. WHO has advocated the use of mobile health (mHealth) as a potentially effective methodology to support patients in the management of their health [6]. MHealth is defined as a “medical and public health practice supported by mobile devices, such as mobile phones” for collecting, managing and sharing health-related data between patients—clinicians and researchers [6]. Therefore, mHealth constitutes a practice that can be effectively adopted for chronic diseases such as diabetes.

As part of the swift and disruptive development and use of technology in the context of public health and health care delivery that has characterised the last decades, there have been an increasing number of mHealth tools piloted in clinical contexts and targeting patients with diabetes [7]. A relevant number of studies tried to prove how communication technologies can increase self-management [8], as well as an effective improvement of clinical outcomes and better care costs [7, 9–11]. Recent systematic reviews and meta-analysis corroborate the effectiveness of mHealth intervention in improving clinical outcomes when compared to usual care in people with diabetes. The vast majority of these studies considered the improvement of the glycosylated haemoglobin (HbA1c) levels as their main outcome. The systematic reviews and meta-analysis of Martos-Cabrera and colleagues [12], Wu and colleagues [13] and Bonoto and colleagues [14], including both type 1 and type 2 diabetes, showed that the use of mobile apps could yield to a significant reduction of HbA1c in comparison to usual care. Authors discussed the importance of further investigating the use of mHealth since current studies regarding mHealth are very heterogeneous by population and mHealth interventions and likely to focus on short-term effectiveness only (< 12 months). The need of conducting more studies on mHealth intervention is supported by other studies results not able to find significant improvements in clinical outcomes, as reported in the systematic review and meta-analysis of Hyun and colleagues [15]. In this systematic review and meta-analysis considering T2DM adult participants and including 14 randomised controlled trials (RCTs), the superiority of using a mobile application (App) or an App with e-coaching on HbA1c levels could only be observed on a limited number of subjects and for a short-term follow-up time [15].

In order to respond to the WHO emphasis on the importance of investing in strategies and public health programmes to prevent and manage diseases through the use of mHealth [16], the Italian Ministry of Health has made funds available to conduct studies focusing on the application of technology in the management of chronic diseases.

This study protocol focuses specifically on one of the Work Packages (WP), i.e. WP4, of a wider project called “Telemedicine for home-based management of patients with chronic diseases and comorbidities: analysis of current models and design of innovative strategies to improve quality of care and optimise resource utilisation: TELEMECHRON study”. WP4 has been approved to be implemented also in the Autonomous Province of Trento (PAT), where, with a slightly lower prevalence of diabetes than in the Italian and global population, currently there are 28.000 cases of people diagnosed with diabetes (5.0% of PAT total population) [17, 18]. The aim of this specific WP is to comprehensively assess an innovative healthcare management system targeting patients with T2DM in non-ideal glycaemic control status. The system is enabled by the use of a mHealth platform called “TreC Diabete”, including an App for participants/patients and a web-based dashboard for health care staff.

### Objectives {7}

#### Research hypothesis

Participants accessing a highly integrated mHealth system can achieve an improved disease control with equal (or even lower) health service utilisation and greater satisfaction (from both patient and healthcare staff perspectives) compared to those not accessing it. The platform is also expected to act as a trigger for a closer interaction among healthcare professionals, such as specialists from other units and to simplify connections between healthcare staff and patient/caregivers.

#### Primary objective

The primary objective of this randomised two parallel groups study is to assess the impact of a novel organisational asset enabled by the use of the TreC Diabete platform on the level of HbA1c within a 12-month follow-up period.

#### Secondary objectives

Secondary objectives include the impact of the mHealth platform use in terms of control of blood pressure and cholesterol, modification of body weight, amount of physical activity, number of hospitalisations, adherence level to prescriptions, improvements of quality of life, satisfaction and usability of the application at different follow-up times within and between groups.

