### Eligibility criteria {10}

Participants must meet at randomisation all the inclusion criteria and none of the exclusion criteria listed in Table 1.

**Table 1 Tab1:** Inclusion and exclusion criteria

Inclusion criteria	Exclusion criteria
• Being diagnosed with T2DM; • Aged ≥ 18 and ≤ 85 years old; • Having an HbA1c level > 7% (53 mmol/mol) and < 12% (108 mmol/mol); • Being able to walk without walking aids; • Having provided written informed consent; • Having a smartphone or a tablet and being able to download the App that will be used to insert the required data	• Having a BMI < 18 kg/m^2^ and > 45 kg/m^2^; • Having a sBP < 100 or > 200 mmHg and/or dBP < 50 or > 120 mmHg; • Being diagnosed with a stage 5 CKD^a^ • Being diagnosed with a NYHA stage IV; • Poor collaboration (i.e. unwilling to modify the actual plan of control and therapy, even if not ideal) for which adherence to the study is unlikely • Having no possibility of using a smartphone or a tablet • Having medical conditions affecting the study participation (i.e. life expectancy < 1 year)

*Abbreviations*: *BMI* body mass index, *CKD* chronic kidney disease, *dBP* diastolic BP, *HbA1c* glycated haemoglobin type A1c, *NYHA* New York Heart Association, *T2DM* type 2 diabetes mellitus, *sBP* systolic BP

^a^based on the glomerular filtration rate according to the CKD-Epidemiology Collaboration equation < 15 ml/min/m^2^ accounting for individual body surface [20]

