#### Secondary outcome measures

Secondary outcome measures are collected at different time point (for specific times of data collection refer to Table 4).Proportion of participants with Hb1Ac < 53 mmol/mol within the two arms;Difference in HbA1c levels between the two arms other than at 12 months;Reporting frequency and number of new hypoglycaemic episodes within the two arms;Proportion of participants reaching the targeted lipid profile (LDL level < 70 mg/dl and non-HLD cholesterol level < 100 mg/dl) and BP levels (sBP < 130 mmHg or > 140 if ≥ 65 years old);Effect on weight, lipid profile and BP levels for the App users;Effect on physical activity performed during the last 7 days prior filling in the questionnaire, for both arm participants;Number of hospitalisation events within the two arms;Number of measurements and level of physical activity with the prescribed activities (body weight monitoring, BP measurements, physical activity) within the two arms;Changes in quality of life (QoL) scores for participants of both arms;Satisfaction and usability score of the App in the intervention arm;

**Table 4 Tab4:** Time schedule of enrolment, interventions and assessments during the study period, adapted from the example template provided by the SPIRIT Group [28]

	Enrolment		Allocation		Post-allocation			Close-out	Personnel and participant involvement	Method of data collection
Timepoint	14 to 21 days prior T0	7 to 14 days prior T0	0 months	0 months (T0)	3 months (T1) (± 30 days)	6 months (T2) (± 30 days)	9 months (T3) (± 30 days)	12 months (T4) (± 30 days)		
ENROLLMENT										
** Informal study information**	x	x							Clinician	Scheduled appointment at clinic
** Eligibility screen**	x	x							Clinician or PI	Scheduled appointment at clinic
** Informed consent signed**		x							Clinician or PI and participant	Face-to-face meeting
** Allocation**			x						Research team	Face-to-face meeting
** Blood tests prescription**		x							Clinician	Face-to-face meeting
** Provide 3 copies of IPAQ questionnaire**		x							Research team	Face-to-face meeting
INTERVENTION										
** App education and instruction manual**				x					Research team	Face to face meeting
** Inform GP of participation**				x					Clinician	Through email
** Help and support with the App use**				x	x	x	x	x	Research team	Phone- email
** App (intervention) monitoring**				x	x	x	x	x	Clinician or research team	Medical dashboard

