### Sample size {14}

The sample size was calculated on the basis of the primary hypothesis (Hb1Ac levels are likely to decrease more in the subjects of the intervention group than for the subjects of the control group at 12 months). A lower variability around the HbA1c mean level is also expected for the subjects in the intervention group when compared to the HbA1c mean level for the subjects in the control group. It was assumed that at 12 months, the mean Hb1Ac level will be 49 (SD ± 3) mmol/mol in the intervention group and 52 (SD ± 7) mmol/mol in the control group. In order to achieve a power of 80% and to keep the significance level at 5%, the sample size was calculated to be 102 (51 in each group) by using Open Epi (a freely accessible software, https://www.openepi.com/Menu/OE_Menu.htm) as depicted in Fig. 1 below. Assuming 20% of drop-out, the required sample was calculated as 120.

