## Statistical methods

### Analysis primary and secondary endpoints {20a}

The analyses of the primary and secondary endpoints will be performed based on the intention-to-treat and as per-protocol approaches. Continuous variables of the two groups will be presented as mean, SD and quartiles, whilst categorical variables will be presented as percentages.

The normality of the distributions is determined by using the normality test of Kolmogorov–Smirnov. To compare the differences between the two groups for continuous outcomes, Student’s *T* test will be used. If the assumption of normality of data distribution does not hold, Wilcoxon’s rank sum test will be used. For repeated measures of continuous variables for which there is an assumption of normality of data distribution, the one-way ANOVA test will be used. If the assumption of normality does not hold, the Friedman test will be used instead of the one-way ANOVA test.

Chi-squared test will be used for categorical outcomes. SAS 9.4 (SAS Institute Inc.) will be used to conduct analyses. For all tests, the significance level is set to 0.05 (2-sided). Professional statisticians ([name]) will conduct all analyses.

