### Trial status

The study protocol was approved by the Local Ethics Committee for Clinical Trials of the Healthcare Trust (APSS) of PAT (Rep. Int. 9453–30/05/2022; project ID: A765 and Rep. Int. 17,489 -11/10/2022; project ID: ES463). The trial is currently ongoing and is planned to finish by September, 2024. Recruitment is planned to be completed by April 2023.

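### Platform impact on secondary outcomes is to be judged within as well as between groups, but within-arm change cannot separate the App from care given to both arms

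*Protocol article*

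**What the plan says.** All places are in the protocol article.

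- **Secondary objectives.** The impact of platform use on blood pressure, cholesterol, weight, physical activity, hospitalisations, adherence, quality of life, satisfaction and usability is to be assessed "at different follow-up times within and between groups".
- **Secondary outcome measures.** One item is "Effect on weight, lipid profile and BP levels for the App users", with no comparator. Several others are worded like "Proportion of participants with Hb1Ac < 53 mmol/mol within the two arms".
- **Analysis primary and secondary endpoints {20a}.** The sentence beginning "To compare the differences between the two groups for continuous outcomes" names Student's t test, with the Wilcoxon rank sum test as fallback; categorical outcomes get a chi-squared test. Separately, for repeated measures of normally distributed continuous variables, "the one-way ANOVA test will be used", with the Friedman test otherwise. No group factor is mentioned for either.
- **Eligibility criteria {10}.** Entry needs HbA1c above 53 and below 108 mmol/mol.
- **Explanation for the choice of comparators {6b}.** Both arms receive best care under the local diabetes pathway.
- **Sample size {14}.** At 12 months it is assumed that "the mean Hb1Ac level will be 49 (SD ± 3) mmol/mol in the intervention group and 52 (SD ± 7) mmol/mol in the control group".
- **Primary outcome measure.** This is a difference in HbA1c between the arms at 12 months.

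**The concern.** Change within the App arm is the sum of whatever the App does and whatever would have happened without it. Here the second part is not small. Every participant gets best care, and for HbA1c everyone is selected on a raised value, so a fall is expected in both arms. A significant within-arm change is then close to guaranteed under quite ordinary conditions and says little about the platform.

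The plan nevertheless names within-group change as one of two bases for judging impact and supplies tests that answer that question. Since Friedman is offered as the fallback for the one-way ANOVA, the factor being tested is evidently time, not group. At stake is what the secondary results may conclude: an improvement in App users' weight, lipids or blood pressure could be presented as an effect although no comparison with controls stands behind it. Correcting the repeated-measures test alone would not cure this, because the fault lies in the within-group question.

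**Working it through.** **1. The plan's own figure.** With SDs of 3 and 7, a difference of 3, 80% power and two-sided 5%:

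n per arm = (3² + 7²)(1.960 + 0.842)² / 3² = 50.58, so 51 per arm and 102 in total. This matches the stated 102, so the 12-month means of 49 and 52 are the ones the design rests on.

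**2. A bound from the plan's figures alone.** Let b be the mean HbA1c at entry. Everyone enters above 53, so b > 53.

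- Control fall = b − 52 > 1
- App-arm fall = b − 49 > 4
- Between-arm contrast = 52 − 49 = 3
- Share of the App arm's fall due to the App = 3 / (b − 49) < 3/4 = 75%

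**3. Assumed entry means.** The article gives no entry mean, so these values are assumptions.

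| Entry mean (assumed) | App-arm fall | Control fall | App share |
|---|---|---|---|
| 55 | 6 | 3 | 3/6 = 50% |
| 60 | 11 | 8 | 3/11 = 27% |
| 65 | 16 | 13 | 3/16 = 19% |

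**4. How often controls alone would show a significant fall.** Paired t test, n = 51, two-sided 5%; the SD of change is assumed to be 7, 10 or 12.

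- Fall of 3 (entry mean 55): power 85%, 56% or 42%.
- Fall of 8 (entry mean 60): at least 99.7% throughout.

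So an arm without the App would often, or almost always, pass a within-arm test on HbA1c.

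**5. Regression to the mean in HbA1c.** For a clinic population with mean μ, truncated to 53–108, the expected fall is (1 − r) × (entry mean − μ), where r is the correlation between two tests. The article gives none of these inputs. Assumed ranges: μ 50 to 60, SD 10 to 14, r 0.6 to 0.9.

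- Smallest: μ = 60, SD 10, entry mean 64.1, r = 0.9, giving 0.1 × 4.1 = 0.4.
- Middle: μ = 55, SD 10, entry mean 61.8, r = 0.8, giving 0.2 × 6.8 = 1.4.
- Largest: μ = 50, SD 14, entry mean 63.1, r = 0.6, giving 0.4 × 13.1, or 5.3 with the unrounded entry mean.

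The range of 0.4 to 5.3 mmol/mol straddles the planned effect of 3.

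**6. Outcomes other than HbA1c.** The article gives no expected control course for weight, lipids, blood pressure or activity, so no size can be computed. The argument there is one of design: care common to both arms enters each arm's change, and only the randomised contrast removes it.

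**The case against.** The strongest reply is that the trial is already comparative where it matters. The research hypothesis compares participants with and without access, the design is a randomised superiority trial, the primary outcome and the HbA1c differences at other times are between arms, and between-group tests are named. Reporting within-arm change beside the randomised contrast is ordinary, and whether it carries a p-value is often settled in the analysis plan. This limits the point to secondary readings. It does not remove it, because the objective itself names within-group assessment as evidence of impact and one outcome has no comparator at all.

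Four stronger readings are tempting and are not supported.

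- **That the items worded within the two arms mean change from baseline.** Hospitalisations and hypoglycaemic episodes share that wording, and Table 4 has no baseline collection for either. The natural meaning is that they are counted in each arm. Quality of life is worded for both arms' participants.
- **That the App would be credited with a 91-point rise in the proportion below 53.** Under normality the plan's figures give Φ(4/3) = 91% of App participants and Φ(1/7) = 56% of controls, against 0% at entry and a between-arm difference of 35 points. Nothing in the article says the rise from zero would be reported as the effect.
- **That the entry rule distorts every secondary outcome.** HbA1c is not in the list of secondary objectives. Regression to the mean from this rule acts directly on HbA1c, and on other outcomes only through their correlation with it.
- **That season invalidates the comparisons.** Registration on 29 November 2022 preceded inclusion, and "Recruitment is planned to be completed by April 2023", so the window is at most 152 days (to 30 April). No start date or seasonal effect size is given. At 12 months participants return to about the same time of year, so season could affect within-arm readings only at 3, 6 and 9 months, for HbA1c, weight, vital signs and the IPAQ. Lipids, SF-12, MMAS-4 and DASI are taken only around baseline and at 12 months.

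**Conclusion.** The concern holds for the secondary outcomes. As written, the plan allows platform impact to be judged from single-arm change, and that change cannot distinguish the App from best care in both arms or, for HbA1c, from selection on a raised value.

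On the plan's own means the App accounts for less than 75% of the App arm's HbA1c fall. This bound needs only that the baseline value is the one that met the entry rule and that the control fall stands for what the App arm would have shown without the App. The shares of 50%, 27% and 19%, the paired-test probabilities and the regression range all depend on the stated assumptions and are illustrations.

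The primary outcome, its power and the planned between-arm comparisons are not affected. The change is worth making, but it does not threaten the trial's main conclusion.

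**What to change.** - **Secondary objectives:** base impact on the between-group comparison only.
- **Secondary outcome measures:** restate the App-users item on weight, lipids and blood pressure as a between-arm difference at the same time point. Clarify that the items worded within the two arms are measured in each arm and compared between arms.
- **Analysis section:** analyse repeated measures with a group comparison, for example a group-by-time term, in place of a test of time alone.
- **Reporting:** present within-arm change descriptively, with no conclusion on effect. Satisfaction and usability (SUS), which exist only in the App arm, properly stay single-arm and descriptive.

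This costs wording and a modest change of model. It needs no new data, visits or participants. All that is given up is claims of within-arm significance.
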